#### Primary outcome

The study primary outcome is the change in the number of teeth with untreated dental caries in both primary and permanent teeth over 12 months. The underlying assumption of the selected primary outcome is that students in the intervention group will visit a dentist during the trial period and as a result will have fewer untreated decayed teeth than those in the comparison group. While the use of a clinical outcome might be perceived more sensitive to services provided after referral, its use is deemed appropriate for this trial as the students will be referred to a specific institution with a system in place to handle those referred.

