#### Secondary outcomes

The change in the proportion of children having teeth with untreated caries and the change in the proportion of children who reported visiting a dentist (as reported by parents and children) during the duration of the trial will be the secondary outcomes.

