#### Between-group comparisons

A comparison of demographic (sex, age), socioeconomic (family income, parental education) and behavioural characteristics (tooth-brushing frequency, dental attendance pattern, last dental visit, reason for last dental visit, use of fluoridated toothpaste and sugars intake) and caries levels in deciduous and permanent teeth between both intervention groups will be carried out using the chi-square test for categorical variables and a *t* test for continuous variables.

We will report absolute and relative measures of effect; that is, absolute and relative difference in means for continuous outcomes (change in number of teeth with untreated caries) and risk differences and relative risks for dichotomous outcomes (changes in the proportions of children having teeth with untreated caries and visiting the dentist). For the primary outcome (change in number of teeth with untreated caries), negative binomial regression will be used to estimate relative differences (incidence rate ratios) and predictive margins to estimate absolute differences between intervention groups. This analytical technique will allow accounting for stratification of the sample, clustering of children within schools and any baseline socioeconomic and behavioural differences between trial groups. For secondary outcomes, log-binomial regression will be used to estimate relative risks for the change in the proportions of children with untreated dental caries and who visited the dentist. Predictive margins will also be used to estimate absolute differences in each secondary outcome. Intention-to-treat analysis will be used to handle missing values in categorical outcomes. Multiple imputation will be considered as an option for continuous outcomes.

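### The primary model (negative binomial, incidence rate ratio) does not match the primary outcome as defined, a change in tooth count that takes both signs

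*Protocol article*

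**What the plan says.** The Primary outcome section defines the outcome as "the change in the number of teeth with untreated dental caries in both primary and permanent teeth over 12 months", and the Abstract gives the same definition. The expected effect, in the same section, is that intervention children "will have fewer untreated decayed teeth than those in the comparison group".

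Under Between-group comparisons the protocol promises "absolute and relative difference in means for continuous outcomes (change in number of teeth with untreated caries"), so the change is classed as continuous. It then assigns the model to that same change: "For the primary outcome (change in number of teeth with untreated caries), negative binomial regression will be used to estimate relative differences". The relative measure is the incidence rate ratio, and predictive margins supply the absolute difference. The factors this technique is said to account for are stratification, clustering within schools, and baseline socioeconomic and behavioural differences. Baseline caries is not mentioned there.

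For the secondary outcomes, "log-binomial regression will be used to estimate relative risks for the change in the proportions of children with untreated dental caries", and likewise for dental visits. The Secondary outcomes section words the visit outcome as "the change in the proportion of children who reported visiting a dentist" over the trial.

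**The concern.** A negative binomial response must be a non-negative whole number. A change score is not one, and this trial hopes to make it negative. An incidence rate ratio built from two mean changes has a second problem: it depends on where the comparison group's mean change lies relative to zero, not only on the benefit achieved.

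Since the stated pairing cannot be run as worded, the analyst must substitute something. Setting negative changes to zero would score a child whose decayed teeth were all treated the same as a child with no change. Dropping negative changes would remove the children who benefited. Switching the response or the model after follow-up would leave the only primary analysis open to choice made with the data in view.

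**Working it through.** **The plan's own figure.** No stated number tests this point directly. The nearest is the sample size, set on a 0.50-tooth difference in number of teeth. The standard deviation is not given. Assuming 1.5, n per group = 2(1.96 + 0.84)² × 1.5² / 0.50² ≈ 142; times the design effect 1 + 74 × 0.03 = 3.22 this is 457, against 455 stated. That calculation is for a difference in means. It neither supports nor weakens the point below.

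**Step 1: sign of the response.** Let D = count at 12 months minus count at baseline.

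- Under Trial interventions, screened-positive children in both groups are referred. A child with 3 untreated teeth, 2 then treated and none new, has D = −2.
- Screened-negative children stay in the trial and start at 0, so D ≥ 0. One new lesion gives D = +1.

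Both signs occur in one sample. Reversing the subtraction turns −2 into +2 but +1 into −1. The negative binomial probability of any negative value is exactly 0, so one such child makes the likelihood zero.

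**Step 2: how many children.** The document gives no mean, dispersion or correlation, so these are ranges under assumptions.

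| Assumed model | Share with D < 0 |
|---|---|
| Counts redrawn at 12 months around a child-specific rate, means 1 to 3, correlation 0.5 to 0.64, no effect | 28% to 39% |
| Same, with a 25% reduction | 32% to 50% |
| Lesions persist unless resolved (10% to 40%), equal new caries, no effect | about 8% to 32% |
| 16 schools × 63 children, 25% v 40% of decayed teeth treated, new caries added, 8 scenarios | 16% to 43% |

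In the last set, 21% to 23% were negative with the sign reversed. Negative binomial fits to the change score did not converge or give a finite log-likelihood in any of 16 attempts (8 scenarios, both signs).

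Hand check of the lowest first-row value: with mean 1 and an exponential child-specific rate, P(no change) = 1/√(3² − 2²) = 1/√5 = 0.447. So P(D < 0) = (1 − 0.447)/2 = 0.276, or 28%.

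**Step 3: ratio of mean changes.** Hold the benefit at the protocol's 0.50 teeth and vary an assumed comparison-group mean change.

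| Comparison | Intervention | Ratio |
|---|---|---|
| +0.60 | +0.10 | 0.17 |
| +0.10 | −0.40 | −4 |
| 0 | −0.50 | undefined |
| −0.10 | −0.60 | 6 |
| −1.00 | −1.50 | 1.5 |

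The same benefit appears below 1, above 1, negative or not at all. A log-link model cannot produce the negative or undefined rows.

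**Step 4: secondary outcomes.** A change in a proportion belongs to a group, whereas a log-binomial model needs a yes/no value per child. Those values are collected: caries status at both examinations and, under Data collection, dental visits asked in the previous 12 months at baseline and since the last contact at follow-up.

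**The case against.** The strongest reply is that 'change' is loose wording. The Between-group comparisons section never says that the response is each child's difference score. The expected effect under Primary outcome and the sample-size target both describe a between-group comparison of numbers of teeth. Change could also be carried by a group-by-time term on the two examinations, whose exponent is a legitimate rate ratio. A negative binomial model of that kind, with generalised estimating equations clustered on school, converged in 50 of 50 simulated datasets.

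This shows that the data can support a negative binomial analysis. It does not show that the protocol specifies one. The definition as a change recurs in the Abstract, under Primary outcome and in the sentence that names the model. The two rescue readings also target different quantities: a ratio of 12-month means, or a ratio of within-group ratios. They agree only when baseline means are equal, and the text chooses neither. Nor is this detail left to an analysis plan, because the protocol names both the response and the model and the two do not fit.

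Three stronger inferences are not supported:

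- **That the secondary models cannot be fitted.** Each child's binary status is available, so the fault is one of wording.
- **That leaving out baseline caries is a separate error.** The factors listed are not presented as a closed set, and covariate detail is commonly settled elsewhere. Baseline count matters here because it is the natural way to keep the notion of change once the response is the 12-month count.
- **That a particular percentage of children would be lost or mis-scored.** Every percentage above rests on assumed distributions.

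**Conclusion.** The point holds for the primary outcome. As written, a signed change is paired with a distribution that excludes negative values and with a ratio that has no stable meaning for changes. This follows from the definitions and the trial's rationale and needs no distributional assumption. Only the size of the affected share, roughly 8% to 50% across the simulations, does.

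A reader might infer that the trial cannot deliver a valid primary analysis. It can: the counts are collected at both examinations, and the defect lies in the stated response. It still needs correcting because it concerns the only primary analysis and the document offers no passage that resolves it. The secondary outcomes need a lesser clarification.

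**What to change.** Under Between-group comparisons, state that the primary response is each child's number of teeth with untreated caries at 12 months, primary and permanent combined. Analyse it by negative binomial regression that accounts for clustering by school and adjusts for baseline count and area stratum. Report the incidence rate ratio and, from predictive margins, the difference in mean teeth. With equal expected baselines under randomisation, the difference in 12-month means equals the difference in mean change, so the 0.50-tooth target carries over.

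For the secondary outcomes, state that the log-binomial models use 12-month binary status (any untreated caries; dental visit during the trial), adjusted for the same variable at baseline.

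Cost: no new data. The outcome wording in the Abstract, Primary outcome, Secondary outcomes and Between-group comparisons sections, and the registry entry, must be aligned and the change dated; this is the small downside. Recruitment began on 20 November 2017, so 12-month data start around November 2018, after protocol version 3 (13 March 2018). That left time to amend before follow-up.

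A convergence fallback is worth naming. In 8 simulated scenarios the recast count model gave finite rate ratios of 0.79 to 0.88, but the optimiser flagged non-convergence in 4. Modified Poisson regression can serve the same purpose for the log-binomial models.

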### Setting and participants

The trial will be conducted across 16 primary schools in Riyadh city, Saudi Arabia. A list of all governmental primary schools in Riyadh city, Saudi Arabia, will be obtained from the Ministry of Education and stratified according to area (schools located in high-socioeconomic and low-socioeconomic areas). Schools with in-house dental clinics and participating in any dental screening/preventive programme will be excluded from the trial.

Children in selected primary schools will be considered eligible to join the trial if they meet all inclusion criteria and none of the exclusion criteria.

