### Data analysis

#### Justification of sample size

Based on a previous relevant study [15], a sample size of 910 children (455 in each trial group) is required to detect a 0.50-unit difference in the number of teeth with untreated caries between the conventional screening group and specific screening group, assuming 80% statistical power, 5% significance level and intra-class correlation coefficient (ICC) for dental caries at school level of 0.03. The total sample size will be rounded up to 1010 (505 in each group) to allow for a dropout rate of up to 11%. After compensating for the clustering of children within schools, there will be six clusters per group, each cluster will include at least 75 participants.

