#### Supplemental analysis

Subgroup analysis will be conducted to explore the effectiveness of school-based dental screening on primary and secondary outcomes among specific subgroups. To that end, we will compare outcomes between the two trial groups among children who were screened positive, and then, among those who reported being regular attenders at baseline.

Comparisons will also be reported stratified by area (high and low socioeconomic status) and dentition (number of teeth with untreated caries in primary or permanent teeth).

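### The 80% power stated for six schools per group appears to ignore school-level degrees of freedom (about 71% on a t reference if the SD is 1.5), and the clustered tests name no small-sample reference

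*Protocol article*

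**What the plan says.** Under Justification of sample size the protocol states that "a sample size of 910 children (455 in each trial group) is required to detect a 0.50-unit difference", "assuming 80% statistical power, 5% significance level and intra-class correlation coefficient (ICC) for dental caries at school level of 0.03". The calculation is attributed to an earlier study; no SD is given. The same paragraph adds that "there will be six clusters per group", each of at least 75 children. That makes 12 schools.

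Under Setting and participants the number differs: "The trial will be conducted across 16 primary schools in Riyadh city". The Abstract also gives 16. At the 1:1 allocation under Trial design this would be eight per group.

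Under Between-group comparisons, the primary outcome is to be analysed by negative binomial regression and the secondary outcomes by log-binomial regression. Of the former the protocol says: "This analytical technique will allow accounting for stratification of the sample, clustering of children within schools". It names no variance estimator, random effect, reference distribution, degrees of freedom or small-sample correction, and it rules none out.

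**The concern.** Schools are the randomised units. With 12 or 16 of them, the between-school variance is estimated from few units, and the treatment contrast should be referred to a t distribution on roughly the number of schools minus two, or one fewer if the area stratum is fitted. A calculation with normal quantiles treats that variance as known and so overstates power. The Discussion says what will be concluded if no benefit is shown, so a type II risk of 29% in place of 20% would matter.

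The analysis raises a related question. Neither regression model handles clustering by itself; that depends on the variance estimator and reference distribution added to it. A common choice, a cluster-robust standard error with a z reference, rejects too often with this few schools. The Discussion also says that a positive result would support national implementation, so control of false positives matters too.

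**Working it through.** **Inputs.** From Justification of sample size: 455 per group, difference 0.50 teeth, 80% power, 5% significance (taken as two-sided), ICC 0.03, six schools per group, 75 children per school. From Setting and participants: 16 schools. Not in the document: the SD, which is back-solved below.

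**Step 1. Reproduce the stated size.**
- Design effect: 1 + (75 − 1) × 0.03 = 3.22.
- Unclustered size implied: 455 / 3.22 = 141.3 per group.
- SD implied by normal quantiles: 0.50 × √(141.3 / 2) / (1.960 + 0.842) = 1.500.
- Forward check with SD 1.5: 2 × (1.5 × 2.8016 / 0.50)² = 141.28; 141.28 × 3.22 = 454.9, against 455 stated. A one-sided test gives about 361 and does not match.

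**Step 2. Power at SD 1.5, keeping 455 per group.** With k schools of m children per group, SE = SD × √(2 × DE / (k × m)). The t-based power uses the noncentral t with noncentrality 0.50 / SE.

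| Schools | m | DE | SE | 0.50/SE | Power, z | Power, t on 2k − 2 df | Power, t on 2k − 3 df |
|---|---|---|---|---|---|---|---|
| 12 (6 per group) | 75.8 | 3.245 | 0.179 | 2.79 | 79.7% | 71.1% (10 df) | 70.1% (9 df) |
| 16 (8 per group) | 56.9 | 2.676 | 0.163 | 3.07 | 86.7% | 81.5% (14 df) | 81.1% (13 df) |

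Retaining all 505 children per group in 12 schools raises the 10 df figure only to 72.4%.

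**Step 3. Range for the unstated SD** (same formulas, t on 10 df and 14 df).

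| SD | 12 schools | 16 schools |
|---|---|---|
| 1.35 | 80% | 89% |
| 1.40 | 77% | 86% |
| 1.50 | 71% | 82% |
| 1.60 | 66% | 76% |

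Eighty per cent is reached at an SD of about 1.35 with six schools per group and about 1.53 with eight.

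**Step 4. Type I error if 1.96 were used without correction.**
- Analytic guide, P(|t| > 1.96): 7.8% on 10 df, 7.0% on 14 df.
- Simulated negative binomial regression under the null, cluster-robust Wald z, 2,000 runs per setting, ICC 0.03: 8.7–9.5% with 12 schools of 75 and 6.9–8.6% with 16 schools of 57.
- A separate gamma-Poisson simulation with 20,000 replicates: 8.6–9.2% with 12 schools and 7.8–8.3% with 16.
- The negative binomial simulation with a t reference in place of z: 5.4–6.6% with 12 schools and 4.9–5.6% with 16.

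**The case against.** The SD is not stated, and the study it came from is not available here. Solving for the SD under normal quantiles and then citing the match as evidence of normal quantiles is partly circular: one equation with one unknown can always be satisfied. A t-based calculation on 10 df also gives 80% at an SD of about 1.35. This stands. The round value 1.5 and a match to within 0.1 child are suggestive, not proof, and a reader should not conclude that 455 can come only from normal quantiles.

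The shortfall also disappears for the trial described elsewhere. The Abstract and the Setting section both say 16 schools, and on that number t-based power is about 81% at SD 1.5. This stands too: the documents do not support saying that a 16-school trial misses its stated power. It does not rescue the sample-size paragraph, which attaches its 80% to six schools per group.

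On the analysis, a reader might infer that the plan uses a large-sample test and will breach the 5% level. The text does not say so. It is silent on the estimator and reference distribution, its wording fits design-based inference with a t reference equally well, and an analysis plan may settle the matter. The inflation is therefore conditional.

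It is tempting, finally, to extend the argument to the supplemental analyses ("Comparisons will also be reported stratified by area"), where a simulated type I error of about 12% arises if each area holds eight schools. The protocol gives no number of schools per area and attaches no confirmatory claim to these comparisons, so that figure carries no weight here.

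**Conclusion.** The power point holds for the design that the sample-size paragraph describes. With SD 1.5 (assumed) and ICC 0.03, six schools per group give about 71% on a t reference (70% if one degree of freedom goes to the area stratum), about nine points below the stated 80%. With 16 schools the power is about 81%. The result depends on the SD: an SD of about 1.35 would give 80% with 12 schools.

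The analysis point holds only as a conditional safeguard. An uncorrected z or robust Wald test would have a type I error of about 7–9% for the primary and secondary comparisons; a t reference brings it close to 5%. Settling on 16 schools does not remove this, since the uncorrected error there is still about 7% or more. Both changes should be made; neither shows that the trial as run will fail.

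**What to change.** - **Sample-size section.** Reconcile 12 with 16 schools. Restate the power with the t distribution on school-level degrees of freedom, the actual number and size of schools, and the SD used with its source.
- **Between-group comparisons.** State that the between-arm tests of the primary and secondary outcomes use a small-sample method: for example, a bias-corrected cluster-robust variance with a t reference on schools minus strata minus 1 degrees of freedom (13 with 16 schools and two areas, 9 with 12). A school-level permutation test stratified by area is an alternative.
- **By-area comparisons.** If they are tested at all, label them as supplemental and report how many schools each area contributes.

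The cost is a few sentences and lines of code, with no change to data collection. The drawback is wider intervals: with 16 schools the critical value is 2.16 instead of 1.96, and 2.16 / 1.96 = 1.10, so about 10% wider before any bias correction of the variance.

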**Methods:**

This is a cluster randomised controlled trial comparing referral of screened-positive children to a specific treatment facility (King Saud University Dental College) against conventional referral (information letter advising parents to take their child to a dentist). A thousand and ten children in 16 schools in Riyadh, Saudi Arabia, will be recruited for the trial. Schools (clusters) will be randomly selected and allocated to either group. Clinical assessment for dental caries will be conducted at baseline and after 12 months by dentists using the World Health Organisation (WHO) criteria. Data on sociodemographic, behavioural factors and children’s dental visits will be collected through structured questionnaires at baseline and follow-up. The primary outcome is the change in number of teeth with untreated dental caries 12 months after referral. Secondary outcomes are the changes in the proportions of children having untreated caries and of those who visited the dentist over the trial period.

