There will be 12 dentists doing the fieldwork under the supervision of the principal investigator. Each fieldwork team will consist of an examiner who will perform clinical examinations and a recorder who will register codes in examination forms. Individuals will switch roles to minimise visual fatigue. They have been trained and calibrated before the beginning of the trial. Mean Kappa values for inter- and intra-examiner reliability in caries diagnosis at tooth level were 0.78 and 0.86, respectively. The principal investigator will hand over referral letters to screened-positive children in girls-only schools (instructing them to put them in the school bags and taking them to their parents). A male organiser, who will not be involved in dental examinations, will do the same in boys-only schools.

Clinical examinations for dental caries will be performed according to WHO criteria that defines dental caries at the caries into dentine threshold [20]. No radiographs will be taken. Examinations will be conducted similarly at baseline and follow-up, with children sitting on a school chair, using headlamps, plane mouth mirrors and a periodontal probe. Teeth will not be brushed or professionally cleaned before examination but cotton wool rolls/buds and the periodontal probe will be used, respectively, to dry the surfaces and remove moisture/debris to facilitate visual inspection. Standard infection control measures will be in place.

After clinical examinations at baseline and follow-up, 10% of participants will be re-examined by the same fieldwork team to assess intra-examiner reliability. After clinical examinations in the follow-up assessment (at 12 months) screened-positive children in both trial groups will be referred to KSU-DC (close-out procedure).

Given the training and calibration of examiners in caries assessment, the probability of having false-positive cases is minimal. Upon referral, a standard dental check-up is always conducted as part of the treatment plan where any false-positive cases will be identified. If that occurs, the dentist will inform parents that upon further examination no treatment is required.

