The selected study design addresses some of the methodological limitations of previous studies [7, 8]. Data collection on participants’ socioeconomic and behavioural factors will help accounting for baseline differences between the two trial groups (if they are unbalanced after randomisation) that might impact use of dental services [21]. However, this study must be conducted with relatively limited resources as part of PhD project and will probably not answer all relevant questions on the effectiveness of school dental screening in Saudi Arabia. Future research should build upon what we are starting in this study, by looking into cost-effectiveness analysis and reasons behind any lack of effectiveness. A national study could also provide more information on effectiveness in different parts of the country.

Finally, it is worth noting that the education system in Saudi Arabia is segregated by children’s gender. Due to cultural restrictions, female dentists cannot access boys-only schools and vice versa. Although we have recruited and trained separate teams for accessing boys- and girls-only schools, access to both types of schools are heavily dependent on approval from the Ministry of Health as the principal investigator, who will oversee the entire fieldwork, is female. This might result in a male-to-female ratio different to 1-to-1.

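### The covariates named for the primary model omit the child's baseline untreated-caries count, which costs precision and leaves the estimate exposed to whatever chance baseline gap arises between arms

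*Protocol article*

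**What the plan says.** All references are to the protocol article.

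- **Primary outcome** defines the endpoint as "the change in the number of teeth with untreated dental caries in both primary and permanent teeth over 12 months".
- **Abstract, Methods:** "Clinical assessment for dental caries will be conducted at baseline and after 12 months by dentists". **Data collection** adds: "Examinations will be conducted similarly at baseline and follow-up". Every examined child therefore has a baseline count taken by the same method as the outcome.
- **Between-group comparisons** gives the primary model: "negative binomial regression will be used to estimate relative differences (incidence rate ratios"), with predictive margins for the absolute difference. It says the technique will allow "accounting for stratification of the sample, clustering of children within schools and any baseline socioeconomic and behavioural differences between trial groups".
- Baseline caries appears in the same section only as a characteristic to be tested between arms: "caries levels in deciduous and permanent teeth between both intervention groups will be carried out using the chi-square test" or a t test. It forms its own category there, apart from the socioeconomic and behavioural ones, and the sentence on the model does not carry it forward.
- **Discussion** repeats the narrower set, and ties adjustment to imbalance being present after randomisation: "Data collection on participants’ socioeconomic and behavioural factors will help accounting for baseline differences between the two trial groups".

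**The concern.** The baseline value of the outcome is usually the strongest predictor of its follow-up value. Here it is already collected, yet it is absent from the adjustment set that the protocol states.

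Taking a difference from baseline looks like adjustment but is not. A child with no decayed teeth at baseline can only stay level or get worse, while a child with many has the most to lose. Change is therefore negatively related to baseline, and a baseline difference between arms carries into the change comparison. If the negative binomial model is in practice fitted to the follow-up count, the baseline count enters nowhere.

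Schools are allocated by simple randomisation within two area strata, and there are few of them: 16 in Setting and participants, six per group in the sample-size section. Within strata nothing balances the arms on caries. At stake are power that could be had at no cost, and an estimate that moves with the luck of the allocation.

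**Working it through.** **Inputs from Justification of sample size:** difference 0.50 teeth, power 80%, significance level 5% (taken as two-sided), ICC 0.03, 455 children per group, six clusters per group of at least 75. **Not in the document, so assumed:** the SD, and rho (shown at 0.3, 0.5 and 0.7). Equal variance at both visits and the same rho and ICC at child and school level are also assumed.

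**1. Reproduce the plan's figure.**
- Design effect = 1 + (75 − 1) × 0.03 = 3.22.
- n per group = 2 × [SD × (1.96 + 0.84) / 0.50]² × 3.22.
- With SD 1.5 this is 141.3 × 3.22 = 454.9, that is 455. An SD of 1.25 gives 316 and 1.75 gives 620. The stated size therefore implies an SD of about 1.5.
- The text does not say whether this is the SD of the count or of the change.

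**2. Variance under each analysis**, in units of the single-visit variance:
- change score: 2(1 − rho)
- follow-up count alone: 1
- adjusted for baseline: 1 − rho²

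Adjusted relative to change is (1 − rho²) / [2(1 − rho)] = (1 + rho)/2, that is 0.65, 0.75 and 0.85 at rho 0.3, 0.5 and 0.7. This is below 1 for any rho below 1, so the direction does not depend on the assumptions about size.

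**3. Power at 455 per group in six schools** (normal approximation). SE = SD × √(2 × 3.22/455) = 0.119 × SD, and power = Φ(0.50/SE − 1.96).

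| rho | If 1.5 is the SD of the change: change → adjusted | If 1.5 is the SD of the count: change → adjusted |
|---|---|---|
| 0.3 | 80% → 93.5% | 66% → 84% |
| 0.5 | 80% → 90% | 80% → 90% |
| 0.7 | 80% → 86% | 95% → 97.5% |

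The two readings agree only at rho 0.5, where 2(1 − rho) = 1. Using t on 10 df in place of the normal, the rho 0.5 row becomes 71% → 83%. At rho 0.7 with the SD read as that of the count, the gain on t is about 4 points, against about 2 on the normal.

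**4. Chance baseline gap between arms** (SD 1.5 and ICC 0.03 at baseline).
- Six schools per group: SE = 0.119 × 1.5 = 0.18. P(gap of 0.25 or more in either direction) is about 16%.
- Eight schools per group, 455/8 = 56.9 children each: design effect = 1 + 55.9 × 0.03 = 2.68, and SE = 1.5 × √(2 × 2.68/455) = 0.16. The probability is about 12%.

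**5. What a gap does to the estimate.** If the intervention arm starts g teeth higher:
- change score moves by −(1 − rho) × g
- follow-up count alone moves by +rho × g
- baseline-adjusted estimate moves by about 0

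For g = 0.25 and rho 0.5, the change estimate shifts by 0.5 × 0.25 = 0.125 teeth, a quarter of the 0.50 target.

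**6. Simulation check** (normal outcome, eight schools of 57 per arm, ICC 0.03, rho 0.5, true effect −0.50, 4000 runs). Averaged over all runs, all three estimators give about −0.50. Their empirical SDs are 0.159 (change), 0.160 (follow-up) and 0.138 (adjusted). In the 11% of runs where the intervention arm began more than 0.2 teeth higher, the means were −0.64, −0.36 and −0.50.

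**The case against.** **The list may not be closed.** The model sentence says what the technique will allow, the article is condensed, and a final covariate list often sits in an analysis plan. This stands in part: a reader might infer that baseline caries is deliberately excluded, and the document does not say so. But the article does state an adjustment set, and its Discussion repeats the socioeconomic and behavioural part. Followed as written, baseline caries is left out; read as open, the most prognostic measured variable is left to a later choice.

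**Bias.** A reader might infer that the primary comparison is biased. It is not: over all randomisations the unadjusted change estimator is unbiased, as the simulation shows. The shift is conditional on the gap that happens to occur. Nor is a large gap likely: one of 0.25 teeth or more is absent in 84% to 88% of allocations. Because area is stratified in allocation and analysis, those probabilities may also be towards the upper end.

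**Size of the gain.** It is tempting to quote one power range. The sample-size text speaks of the number of affected teeth and an ICC for caries, which reads more naturally as the count. On that reading the gain at rho 0.7 is only about 2 points (normal). No single range is supported.

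**Model form.** The figures are Gaussian, while the plan names negative binomial regression. They indicate scale and are not predictions for that model. The need for the covariate does not depend on this, but the direction of the shift does: it reverses if the follow-up count is modelled.

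**Attendance.** Last dental visit is already among the behavioural characteristics, so that outcome has no real gap.

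**Conclusion.** The point holds as a precision gain plus protection against a realised chance imbalance. The stated model terms omit a baseline measure that the trial already collects, and subtraction does not make up for it. At rho 0.5 adjustment is worth about 10 points of power (80% to 90%, normal, six schools per group). At rho 0.3 and 0.7 the gain runs from about 2 to 18 points, depending on rho and on which quantity the back-solved SD describes. A gap of 0.25 teeth or more, expected in 12% to 16% of allocations, would move the change estimate by 0.125 teeth at rho 0.5. All sizes rest on an assumed SD of about 1.5, an assumed rho and a normal approximation. The documents do not support a claim of systematic bias. This is an improvement that should be made; it does not invalidate the design.

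**What to change.** In Between-group comparisons, state that the primary model includes the child's baseline number of teeth with untreated caries as a fixed, pre-specified covariate, whatever the baseline comparison shows. Keep the stratum and school-clustering terms. Include baseline untreated caries in the same way in the model for the proportion of children with untreated caries. For attendance, only make the inclusion of baseline last dental visit unconditional. Report the adjusted estimate with its predictive margin as primary.

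The cost is a sentence or two, written before outcome data are analysed. It needs no new data and no more children, and uses at most one model degree of freedom per outcome. The incidence rate ratio or relative risk is then read conditional on baseline, and the predictive margins already planned supply the marginal absolute difference.
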